## Abstract

**Introduction:**

Extended-spectrum β-lactamase–producing Enterobacterales (ESBL-E) pose a major global public health challenge, as they are associated with frequent empirical antibiotic treatment failure and increased patient morbidity and mortality. In this context, contact precautions (CP) have traditionally been recommended for hospitalized patients colonized or infected with ESBL-E to prevent healthcare-associated transmission. However, growing evidence has questioned the effectiveness of this strategy in certain care settings.

The primary objective of this study is to assess the non-inferiority of standard precautions (SP) compared with **clinically triggered** CP in reducing the incidence density of ESBL-E acquisition in acute-care geriatric wards. By doing so, this study aims to inform the evaluation of pragmatic infection prevention policies implemented at the institutional level in vulnerable hospital populations.

**Methods and analysis:**

We will conduct a prospective, two-site interventional study in two geriatric departments of the Metz–Thionville Regional Hospital Center (Metz, France) using an alternating-period (crossover-like) design at the site level, with random allocation of the starting condition (CP first vs SP first).

Patients will be screened for ESBL-E carriage at admission and at discharge. During CP periods, contact precautions are implemented only for patients with clinically detected ESBL-E infections identified through routine clinical cultures; asymptomatic ESBL-E carriage identified through surveillance screening does not trigger contact precautions. During SP periods, patients are managed using SP alone.

The primary outcome is the incidence density of ESBL-E acquisition per 1,000 patient-days. Secondary objectives include species-specific analyses comparing ESBL-producing Escherichia coli and non-E. coli Enterobacterales. The total inclusion period is four years. Incidence rates will be compared using count regression models adapted to clustered period-based data.

## Introduction

### Background and rationale

Multidrug-resistant Gram-negative bacteria (MDR-GNB) pose a major global health challenge in the 21st century [1,2]. Since the early 2000s, the prevalence of third-generation cephalosporin–resistant Enterobacterales has steadily increased worldwide. Extended-spectrum β-lactamase–producing Enterobacterales (ESBL-E) are a major contributor to this rise [3], with numerous outbreaks reported in healthcare settings, particularly in intensive care units (ICU) and long-term care wards, leading to increased morbidity, mortality, and healthcare costs [4,5].

Initially, Klebsiella pneumoniae was the most frequently isolated ESBL-E species, but more recent epidemiological data indicate a growing burden of ESBL-producing Escherichia coli, especially in community settings [6]. In France, national surveillance data have shown a continuous increase in ESBL-E incidence, with incidence density rates now three to four times higher than those observed for methicillin-resistant Staphylococcus aureus (MRSA) [7].

Advanced age is a well-established risk factor for infection [8], largely due to immunosenescence and the high prevalence of chronic comorbidities [9–11]. A multicenter prevalence study conducted in eight French hospitals identified hospitalization in geriatric wards as a significant risk factor for ESBL-E carriage, with 28.2% of geriatric inpatients colonized [12]. Prolonged care and frequent exposure to biological fluids in geriatric settings further increase the risk of cross-transmission.

Elderly inpatients therefore present multiple risk factors for colonization with multidrug-resistant organisms (MDRO), including antibiotic exposure, colonization pressure, and organizational factors such as workload and care density. Several studies have demonstrated associations between staffing constraints, increased workload, and healthcare-associated infection risk [13,14]. Despite this, geriatric wards remain relatively understudied as potential reservoirs of ESBL-E.

Infection prevention and control (IPC) measures are central to preventing nosocomial ESBL-E transmission. Contact precautions (CP) consist of a bundle of measures aimed at limiting cross-transmission, including single-room placement or cohorting, hand hygiene, use of gowns during patient contact, and dedication of noncritical medical equipment [15]. International guidelines generally recommend CP in addition to standard precautions (SP) for patients colonized or infected with multidrug-resistant organisms [16–18].

However, growing evidence suggests that CP may not significantly reduce ESBL-E transmission compared with SP alone in certain healthcare settings [19–21]. Limited screening strategies may lead to underdetection of carriers, thereby reducing the effectiveness of targeted CP. These findings support the rationale for reinforcing universal SP for all patients, regardless of colonization status. Consistent with this approach, French national recommendations allow healthcare institutions to choose between CP- and SP-based strategies, provided that key indicators such as hand hygiene compliance and healthcare-associated infection rates are closely monitored.

The potential benefits of CP must also be balanced against unintended consequences, including increased workload and costs, reduced patient–healthcare worker interactions, and declining compliance during epidemic situations [22–26]. In resource-constrained settings, identifying effective and sustainable infection control strategies is therefore essential.

Several studies support reconsideration of CP use. Observational data from a Swiss university hospital showed low ESBL-E transmission rates in settings with high adherence to SP [27]. A cluster-randomized crossover study in Dutch hospitals demonstrated that CP in multi-bed rooms was noninferior to CP in single rooms for preventing ESBL-E transmission [28]. In addition, a non-inferiority before-and-after study conducted in an ICU at the Metz–Thionville Regional Hospital found that discontinuation of CP did not increase acquisition of MRSA or ESBL-E when high standards of hand hygiene and antimicrobial stewardship were maintained [29].

More recently, a systematic review published in 2023 concluded that discontinuation of CP for patients colonized or infected with ESBL-E had minimal clinical impact and could be safely implemented in acute, noncritical adult care wards. Importantly, pediatric and geriatric settings were not included in these analyses, and no validated guidelines currently explicitly permit CP discontinuation for geriatric inpatients with ESBL-E [30].

To the best of our knowledge, no previous study has evaluated the non-inferiority of standard precautions compared with contact precautions in geriatric care. The GERSP study is therefore the first to address this critical evidence gap in this specific clinical context.

### Study objectives and hypotheses

The primary objective of this study is to assess whether SP alone are non-inferior to clinically triggered CP with respect to limiting cross-transmission of ESBL-producing Enterobacterales in acute geriatric care units.

We hypothesize that discontinuation of CP will not result in a clinically relevant increase in hospital-acquired ESBL-E. Given that the main reservoir of ESBL-E is the gastrointestinal tract, key preventive measures focus on safe handling of excreta and appropriate hand hygiene, which are core components of SP.

The secondary objective is to assess whether transmissibility differs by ESBL-E species, with the hypothesis that cross-transmission is lower for ESBL-producing Escherichia coli than for non-E. coli Enterobacterales.

## Methods and analysis

### Study Setting

The study is conducted at the Metz–Thionville Regional Hospital Center, a bi-site tertiary care institution located in Metz and Thionville (approximately 30 km apart), serving a catchment population of about 600,000 inhabitants.

Two acute-care geriatric departments participate in the study. The geriatric department of Mercy Hospital comprises four units of 11 beds each, and the geriatric department of Bel-Air Hospital comprises two units with 15 and 23 beds, respectively. Both departments provide comparable acute geriatric care and admit older adults from the same hospital catchment area.

### Study design

This is a prospective, bi-site interventional study using an alternating-period (crossover-like) design at the site level.

Each participating site alternates between two predefined infection prevention and control (IPC) strategies—contact precautions (CP) and standard precautions (SP)—across successive study periods. The initial IPC strategy (CP first or SP first) is randomly assigned at the site level.

This pragmatic design was chosen to evaluate IPC policies under real-world conditions while accounting for potential seasonality and operational constraints. The overall study design, including the planned participant flow, is illustrated in Fig 1.

**Fig 1 pone.0353783.g001:**
[figure not shown]
Planned CONSORT participant flow diagram for the GERSP study.

### Patient and public involvement

No patients or members of the public were involved in the design, conduct, reporting, or dissemination plans of this research protocol. The study was designed by clinicians and researchers based on current evidence and institutional priorities in IPC.

### Participants

#### Inclusion criteria.

Patients are eligible for inclusion if they meet all of the following criteria:

age ≥ 65 years;hospitalization in a participating geriatric unit during a study period;affiliation to a social security system;written informed consent obtained within 48 hours of admission, either from the patient or a legal representative.

#### Exclusion criteria.

Patients are excluded if they meet any of the following criteria:

conditions requiring mandatory contact precautions regardless of study period, including carbapenemase-producing Enterobacterales, glycopeptide-resistant *Enterococcus*, *Clostridioides difficile* infection, scabies, or other multidrug-resistant organisms requiring CP according to national guidelines;hospital stay shorter than four days;withdrawal of consent;death during hospitalization.

### Intervention and infection prevention policies

The detailed schedule of enrolment, interventions, and outcome assessments in accordance with SPIRIT recommendations is presented in Fig 2.

**Fig 2 pone.0353783.g002:**
[figure not shown]
Schedule of enrolment, interventions, and assessments (GERSP study).

^a^ Allocation occurs at the site level according to the randomized order of study periods (SP first vs CP first). Participants are exposed to the infection prevention policy in effect during their hospitalization.

Two IPC strategies are compared (Table 1):

**Table 1 pone.0353783.t001:** Description of infection prevention policies during CP and SP periods.

	“CP” period	“SP” period
ESBL-E surveillance screening	Rectal screening at admission and discharge (results not disclosed to ward staff)	Rectal screening at admission and discharge (results not disclosed to ward staff)
Clinical microbiological sampling	Performed when infection is suspected, according to routine practice	Performed when infection is suspected, according to routine practice
Management of clinically detected ESBL-E infection	Contact precautions implemented in addition to standard precautions	Standard precautions only
Training and support	Training and support on SP and CP provided by the infection control team	Training and support on SP and CP provided by the infection control team
Process evaluation	Audits and interviews to assess hand hygiene practices	Audits and interviews to assess hand hygiene practices

#### CP periods.

During CP periods, patients are managed according to SP. In addition, CP (use of gowns, dedicated equipment, and patient cohorting or single-room placement when indicated) are implemented **exclusively** for patients with clinically diagnosed ESBL-E infections identified through routine clinical microbiological cultures (e.g., urine or blood cultures).

Surveillance rectal screening for ESBL-E carriage is performed at admission and discharge for research purposes only. Results of these screenings are not disclosed to ward staff, are not recorded in the electronic medical record, and do not trigger implementation of CP.

#### SP periods.

During SP periods, all patients are managed using SP alone, including hand hygiene, use of personal protective equipment according to anticipated exposure, and environmental cleaning.

### Co-interventions

Throughout the study, indications for CP unrelated to ESBL-E (e.g., carbapenemase-producing Enterobacterales, glycopeptide-resistant *Enterococcus*, *Clostridioides difficile* infection, scabies) are applied identically during both CP and SP periods, in accordance with institutional and national guidelines. Airborne and droplet precautions are implemented whenever clinically indicated, regardless of study period.

To ensure quality support from the IPC team, the two sites will be opened consecutively rather than simultaneously. The periods will be defined as follows, in order to account for potential seasonality (Fig 2):

at
**Bel Air:** March–September, 2023 (**1st study period**), April–October, 2024 (**2nd study period**), April–October, 2025(**3rd study period**), April–October, 2026 (**4th study period**)at
**Mercy:** October 2023 – March, 2024 (**1st study period**), October 2024 – March, 2025 (**2nd study period**), October 2025 – March, 2026 (**3rd study period**), October 2026 – March, 2027 (**4th study period**)

One site will begin with the CP period and the other with the SP period. Throughout the study, indications for CP unrelated to ESBL-E (e.g., carbapenemase-producing Enterobacterales, glycopeptide-resistant Enterococcus, Clostridioides difficile infection, scabies) are applied identically during both periods, in accordance with institutional and national guidelines. Similarly, airborne and droplet precautions are implemented whenever clinically indicated, regardless of study period.

### Outcomes

#### Primary outcome.

The primary outcome is the incidence density of hospital-acquired ESBL-E per 1,000 patient-days, defined as ESBL-E detection at discharge following a negative admission screening.

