#### Blinding organization of surveillance screening results.

Rectal screening for ESBL-E carriage performed at admission and discharge is conducted exclusively for research purposes. Results of these surveillance screenings are not communicated to ward staff during either study period. This approach is intended to prevent behavioral changes that could bias comparisons between infection prevention policies.

Specifically, during CP periods, disclosure of surveillance results could lead to implementation of CP beyond routine practice, whereas during SP periods, knowledge of colonization status could increase vigilance and artificially reduce cross-transmission.

Surveillance screening results are therefore accessible only to the microbiology laboratory, the clinical research support platform, and the IPC team. Results of rectal swabs are not recorded in the electronic medical record and are documented solely in the study case report form (CRF).

Importantly, results of routine clinical microbiological cultures (e.g., urine or blood cultures performed for suspected infection) are communicated to clinical teams as usual and guide antimicrobial prescribing and patient management. Only surveillance rectal screening results performed for research purposes are concealed from ward staff.

Ward staff and patients cannot be blinded to the IPC policy implemented during each period. However, patients are not informed of surveillance screening results, as these are not used for clinical decision-making.

Unblinding of surveillance results occurs only in the event of detection of emerging extensively drug-resistant bacteria (eXDR), in accordance with national “search and isolate” recommendations. In such cases, CP are immediately implemented as required for patient safety.

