### Microbiological samples

Rectal swabs for ESBL-E surveillance cultures are obtained by trained ward nurses within 48 hours of admission and at discharge. Samples are processed in local microbiology laboratories following standardized procedures, including direct plating on chromogenic agar for ESBL-E detection. Antimicrobial susceptibility testing is performed using disk diffusion and interpreted according to CASFM–EUCAST guidelines.

All ESBL-E isolates are stored and sent to the Infection Control Department of Besançon University Hospital for molecular typing using pulsed-field gel electrophoresis. Laboratory staff performing molecular analyses are blinded to study period and IPC strategy.

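### The primary outcome counts a patient with ESBL-E in a clinical culture on arrival as a hospital acquisition whenever the admission rectal swab is negative and the discharge swab positive

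*Protocol article*

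**What the plan says.** The Primary outcome section takes the incidence density of hospital-acquired ESBL-E per 1,000 patient-days, "defined as ESBL-E detection at discharge following a negative admission screening". Under Microbiological samples, "Rectal swabs for ESBL-E surveillance cultures are obtained by trained ward nurses within 48 hours of admission and at discharge", and processing is described as "following standardized procedures, including direct plating on chromogenic agar for ESBL-E detection". No repeat admission swab is mentioned, and Table 2 lists a single baseline rectal screening.

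Clinical cultures are a separate stream. Table 1 gives surveillance screening and clinical sampling their own rows, with clinical sampling "Performed when infection is suspected, according to routine practice" in both periods. The section on blinding of screening results states that "results of routine clinical microbiological cultures (e.g., urine or blood cultures performed for suspected infection) are communicated to clinical teams as usual". Under CP periods, an ESBL-E infection found by such a culture is what triggers contact precautions.

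The Exclusion criteria remove "conditions requiring mandatory contact precautions regardless of study period, including carbapenemase-producing Enterobacterales" and several other conditions. Known ESBL-E carriage or infection is not among them.

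**The concern.** The stated rule gives a wrong answer for an identifiable type of patient. Take someone admitted with an ESBL-E urinary infection: the urine culture on the day of arrival is positive and the rectal swab is negative. In a CP period the ward treats this patient as a recognised source. If the discharge swab is positive, the outcome definition records the same patient as having acquired ESBL-E in hospital. Nothing in the article prevents this, and it runs against the objective of measuring cross-transmission.

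This is not detail left to an analysis plan: the article states the event definition in full. Nor can a negative admission screening be read to include clinical cultures, because Table 1 and the blinding section keep the two apart. The planned molecular typing does not resolve it, because typing is not part of the outcome and a falsely negative admission swab leaves no rectal isolate to compare.

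At stake are the precision of a comparison that rests on very few events and, if admission carriage differs between CP and SP periods, its validity.

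**Working it through.** **Inputs from the article**
- Sample size: 1 acquisition per 1,000 patient-days under CP; margin 1 per 1,000; one-sided alpha 5%; 80% power; 6,178 patient-days, raised to 9,130 by a design effect of 1.48; 954 patients with 15% exclusions.
- Background and rationale: a prevalence study in eight French hospitals, "with 28.2% of geriatric inpatients colonized". This is an inpatient figure, used here only as a proxy for carriage at admission.

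**Assumptions not in the article**
- Sensitivity s of one rectal swab, the same at admission and discharge.
- The two swab results are independent within a carrier.

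**The plan's own figures.** 6,178 × 1.48 = 9,143, close to the stated 9,130. The 6,178 is reproduced only with a one-group variance: 0.001 × 0.999 × 6.18 / 0.001² ≈ 6,176. A two-group calculation gives about 24,706. That is a separate matter: at a fixed length of stay, the ratio of missed carriers to true acquisitions does not depend on total size.

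**Expected true events.** 9,130 × 1/1,000 = 9.1. Analysed patients: 954 × 0.85 = 811. Mean stay: 9,130 / 811 = 11.3 days.

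**What one event weighs.** With an even split, each policy has 4,565 patient-days. One event more in one policy than in the other shifts the difference by 1,000 / 4,565 = 0.22 per 1,000, about a fifth of the margin.

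**Illustration: all missed carriers.** Carriers at admission: 811 × 0.282 = 229. Missed: 229 × (1 − s). Missed and then detected at discharge: 229 × (1 − s) × s.

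| s | Missed | Later detected | Detected per 1,000 patient-days |
|---|---|---|---|
| 95% | 11.4 | 10.9 | 1.2 |
| 90% | 22.9 | 20.6 | 2.3 |

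**Break-even.** Missed carriers exceed true acquisitions when s is below 1 − 9.13 / (811 × carriage):

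| Carriage at admission | Break-even sensitivity |
|---|---|
| 28.2% | 96% |
| 15% | 92.5% |
| 10% | 89% |
| 5% | 77.5% |

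**Precision.** At 28.2% carriage and s = 90%, the observed rate is 0.90 + 2.25 = 3.15 per 1,000. Power is Φ(0.001 / √(2λ/4,565) − 1.645), ignoring clustering. It is 45% at λ = 0.001 and 21% at λ = 0.00315.

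**Bias.** Suppose admission carriage differs by 5 percentage points between CP and SP periods (an assumed value) and s = 90%. The difference shifts by 0.05 × 0.10 × 0.90 × 1,000 / 11.26 = 0.40 per 1,000, or 40% of the margin. The direction depends on which policy's periods have the higher carriage.

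The precision and bias figures cover every missed carrier. Those who also have a positive clinical sample on arrival are a subset whose size the article does not give.

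**The case against.** Several points on the other side stand.

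- **Cancellation.** Statistical methods specifies an absolute rate difference. False events that do not depend on policy add equally to both sides and largely cancel. A reader might infer that they dilute any real policy effect; for this contrast they mostly do not. Wider bounds also make non-inferiority harder, not easier, to conclude.
- **Unknown inputs.** Swab sensitivity is nowhere in the article. The 28.2% is inpatient prevalence and may include carriage acquired in hospital. A carrier missed once may shed little and be missed again, which lowers the count. If the source of the 1 per 1,000 also used swabs, that rate may already contain missed carriers. The phrase "including direct plating on chromogenic agar for ESBL-E detection" leaves room for further laboratory steps. So the tempting reading that the endpoint mainly measures swab sensitivity is not supported: at 98% sensitivity even 28.2% carriage gives only about 4.5 false events.
- **Earlier isolates.** An old isolate does not prove current carriage, and a negative then a positive swab in such a patient can be a true acquisition. This argues against using past records in the primary definition.
- **Policy-dependent sampling.** Clinical samples are taken on suspicion by staff who know the policy, whereas the swab is the same for everyone. Restricting to the first 48 hours limits this risk but does not remove it.
- **Acknowledged limits.** Limitations and interpretation concedes that timing and source are only approximated. It does not mention false-negative admission swabs, and it still presents the incidence estimate as sound.

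None of these answers the specific case of a patient whose arrival culture already shows ESBL-E.

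**Conclusion.** The point holds in a limited form. As written, the definition classes a patient as hospital-acquired when a clinical culture at admission shows ESBL-E, the admission swab is negative and the discharge swab is positive. All three conditions are needed; a reader might infer that every patient with known ESBL-E is counted, but those with a positive admission swab are not.

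The harm is a higher observed rate and a wider confidence bound, set against about 9 expected true events. Bias in SP minus CP follows only if admission carriage differs between policies. That is possible with two sites and staggered periods, but the documents do not show it. The illustrative counts of about 11 and 21 rest on an assumed sensitivity, a proxy prevalence and independent swabs. They are smaller at lower carriage and cover all missed carriers, not only those the laboratory record can identify. The number of wrongly counted patients is therefore unknown. The change is still worth making while the trial is under way.

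**What to change.** - **Primary outcome:** define a patient as at risk only if the admission rectal swab is negative and no ESBL-E was found in any clinical sample taken within 48 hours of admission. Apply the rule identically in CP and SP periods.
- **Sensitivity analyses:** (a) the swab-only definition; (b) a further exclusion of patients with an earlier ESBL-E isolate on the laboratory record.
- **Reporting:** give the number of patients removed by the clinical-sample rule for each period, since clinical sampling may vary with policy.
- **Limitations and interpretation:** add false-negative admission screening, and qualify the statement that the two-swab approach estimates incidence density soundly.

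The cost is an amendment to the wording and a look-up of existing laboratory results, with no new sampling. A few patients leave the at-risk set. The rule removes only missed carriers who have a clinical isolate; the rest stay in the outcome.
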